At the program-level, limited research is available on the influence of program characteristics on obesity management and obesity-related health outcomes. Children and parents who complete a structured lifestyle and behavioural intervention achieve greater reductions in weight status than non-completers [8]. Intervention intensity (e.g., number of clinical contact hours) may be a key determinant of treatment efficacy, but the optimal number of contact hours is uncertain, and the nature of how and with whom these clinical hours are spent is unknown [8]. Our understanding of the effectiveness of program-related factors including intervention modality (e.g., group *vs* individual sessions), disciplinary approach (e.g., unidisciplinary *vs* multidisciplinary), and behavioural techniques (e.g., self-monitoring nutrition/physical activity habits, regular weighing, goal-setting) [24] in managing pediatric obesity remains incomplete. Multi-centre research will allow us to examine the influence of determinants of responsiveness to obesity management in diverse clinical environments that extend across cultures and contexts within the Canadian health care environment [25].

Despite evidence supporting the effectiveness of strategies to manage pediatric obesity [8], little evidence is available regarding the sustainability of changes in health outcomes achieved through behavioural interventions in pediatric obesity as highlighted in multiple systematic reviews [8,9] and reports [26]. A recent systematic review identified four trials that evaluated the maintenance of weight change after lifestyle and behavioural interventions and concluded that improvements in obesity status can be sustained over a 12-month follow-up period [8]. Children with obesity can lose and maintain weight loss up to five [15] and 10 years [27] following family-based lifestyle and behavioural interventions; however, these findings remain unique in the literature and fail to consider potential changes in other factors that are often targeted within interventions (e.g., nutrition, physical activity, cardiometabolic risk factors).

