### Statistical analysis

The results of patient demographics and baseline outcome variables (both primary and secondary) will be summarized using descriptive summary measures, expressed as mean (standard deviation) or median (minimum-maximum) for continuous variables and number (percent) for categorical variables. We will use multi-level or hierarchical modeling to analyze the data to address the primary and secondary aims [36] to determine the relationship between outcomes and individual-, family-, and program-level characteristics (Table 1). We will report the results as the estimate of the measure of association—model coefficients for continuous outcomes, odds ratios (OR) for binary outcomes or hazard ratio (HR) for time-to-event outcomes, corresponding 95% confidence intervals, and associated p-values. We will report p-values to three decimal places with p-values less than 0.001 reported as p < 0.001. All statistical tests will be performed using two-sided tests at the 0.05 level of significance. The Bonferroni method will be used to adjust the level of significance for testing for secondary outcomes to keep the overall level at α = 0.05. We will assess colinearity using the variance inflation factor (VIF) which measures the extent to which the variance of the model coefficients will be inflated. We will consider variables with VIF > 10 colinear and we will exclude them from the analysis [37]. We will perform all analyses using Statistical Analysis System (*SAS*) *version 9.2* (Cary, NC, USA).

Sensitivity analyses will be performed to assess the robustness of the results. First, there is likely to be missing data that will likely increase with time. We will use multiple imputations to handle missing data [38]. Second, there is likely to be high inter-correlations among outcomes. We will use a multivariate analysis of covariance (MANCOVA) approach to analyze all outcomes simultaneously. This method accounts for possible correlations among all outcomes and provides for a global assessment of the impact of each predictor variable with an indication of where differences exist. Third, we will use generalized estimating equations (GEE) assuming an auto-regressive correlation structure to account for possible serial correlation of measurements within a patient overtime [39]. Unlike ordinary linear regression, GEE allows accounting for possible serial correlation of outcomes within a patient over time.

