### Statistical power

Given a sample size of 1,600 and 41 variables or determinants to be included, the ratio of participants to variables is 39:1. Previous studies have shown that a fitted regression model is likely to be reliable and stable when the number of independent predictors is less than the total sample size divided by 20 [40]. Considering 40%, 25% or 15% dropout (n = 960, 1,200, 1,360 respectively), a two-sided test with significant level α = 0.05/4 = 0.0125 gives 90% power to detect a small R-square 0.0313 -0.0442 for 41 determinants. Thus, we have high power to test the effects of the described variables. For secondary hypothesis one (Table 1), we intend to examine three additional outcomes. To account for multiple hypothesis testing two-tailed α = 0.0125, we will continue to have power exceeding 90% to examine the influence of the determinants on the outcome at one year. For secondary hypothesis two, we intend to examine the determinants for sustainability of weight loss. To do so, we will examine the determinants for maintenance or decline of BMI z-score from year one to year two. If we conservatively estimate that at least 30% will have an increase in BMI z-score over that time period, we have 90% power to detect a variable that will increase this by 1.3 fold – and this is true even if we have 40% drop out from our study. Similarly, if the proportion of participants whose BMI z-score increases from year one to year two is higher, our power would be > 90%. Findings from several published trials suggest these assumptions are appropriate [21,41]. For secondary hypothesis three, we will examine the determinants of program drop out within one year of enrollment. We are sufficiently powered to detect an OR of 1.2 if 25% or more of those who commence a program drop out, and to detect an OR of 1.3 if only 15% drop out of the program.

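### Multiple imputation, the only robustness check listed for missing data, says little about outcome-dependent loss of BMI z-scores; a delta-adjusted range should be added to it

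*Protocol article*

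**What the plan says.** The main analysis is fixed under Statistical analysis: "We will use multi-level or hierarchical modeling to analyze the data to address the primary and secondary aims". The same section gives the purpose of the additional analyses: "Sensitivity analyses will be performed to assess the robustness of the results". It then lists three, which Table 1 repeats:

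- Missing data: the section states that "there is likely to be missing data that will likely increase with time. We will use multiple imputations to handle missing data".
- Correlation among outcomes: MANCOVA.
- Serial correlation within a child: "we will use generalized estimating equations (GEE) assuming an auto-regressive correlation structure".

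Only the first is aimed at missing data. Neither place states a missingness assumption or a departure from one.

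Four other parts of the article bear on the point:

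- The Background reports that children and parents who complete a structured intervention "achieve greater reductions in weight status than non-completers", and cites program attrition of 27–73%.
- Statistical power sets three loss scenarios: "Considering 40%, 25% or 15% dropout".
- Data collection plans a separate research visit for children who stop attending the program, and chart retrieval, where possible, when data are missing or a family leaves the study.
- Measurements records clinical status (active, inactive or discharged), clinic hours and visit adherence.

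**The concern.** A sensitivity analysis tests an assumption only if it relaxes or changes that assumption. A multilevel model fitted by likelihood to all available visits is valid when outcomes are missing at random given the data in the model. Ordinary multiple imputation of the outcome from the same data makes the same assumption. The two should give nearly the same answer whether or not the assumption is true.

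The departure of interest is that children whose BMI z-score is never obtained did worse than their observed history predicts. None of the three listed analyses addresses this. MANCOVA deals with correlated outcomes, and unweighted GEE needs a stronger missingness assumption than the multilevel model.

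Two results are most exposed. One is the statement about sustained change over three years, because missing data are expected to grow with time. The other is the coefficient of any determinant that is also related to loss; the third secondary hypothesis holds that determinants of the same kinds predict attrition from the program.

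**Working it through.** **Inputs from the documents.** Sample size is 1,600, with dropout of 40%, 25% or 15% (Statistical power).

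**The plan's own figures.** 1,600 × 0.60 = 960, 1,600 × 0.75 = 1,200 and 1,600 × 0.85 = 1,360, as stated. At α = 0.0125, 41 determinants and 90% power, the noncentral F test gives a detectable R-square of 0.0439 (n = 960) and 0.0311 (n = 1,360), against the stated 0.0442 and 0.0313. These figures are sound, and this point does not affect them.

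**Assumed inputs.** The documents give no difference between lost and retained children. Let delta be the amount by which a child with a missing BMI z-score is worse than predicted from observed data, taken as 0.1 to 0.3 z.

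**Step 1: do the two methods differ when loss depends on the outcome?** One large simulated cohort of 400,000 records per scenario had three visits and a 50/50 binary determinant whose two levels differ by 20 points in loss. Loss affected the last visit. The missing-at-random likelihood estimate was obtained by sequential regression, and multiple imputation used 10 imputations from the same variables. At this size, drawing the imputation parameters makes no material difference.

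| Loss | Delta | True mean change | Likelihood | Imputation |
|---|---|---|---|---|
| 15% | 0.1 | −0.030 | −0.044 | −0.044 |
| 25% | 0.1 | −0.021 | −0.046 | −0.046 |
| 40% | 0 | −0.046 | −0.046 | −0.046 |
| 40% | 0.1 | −0.006 | −0.046 | −0.046 |
| 40% | 0.2 | +0.036 | −0.045 | −0.045 |

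Likelihood and imputation agree to within about 0.001 in every scenario run, biased or not.

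A second simulation used a different design: 150 cohorts of 1,600 per setting, five visits, and 39% lost by 36 months with loss depending on the current unseen change. The true mean change was −0.151. Likelihood and imputation agreed to three decimals and gave −0.169, −0.184 and −0.205 for weak, moderate and strong dependence.

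**Step 2: size for mean change.** Bias = loss × delta.

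| Loss | 0.1 z | 0.2 z | 0.3 z |
|---|---|---|---|
| 15% | 0.015 | 0.030 | 0.045 |
| 25% | 0.025 | 0.050 | 0.075 |
| 40% | 0.040 | 0.080 | 0.120 |

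For scale, with an assumed SD of change of 0.4, the 95% half-width for mean change is 1.96 × 0.4/√960 = 0.025 at 40% loss and 1.96 × 0.4/√1,360 = 0.021 at 15% loss. The smallest entry lies inside its half-width; all entries in the 40% row lie outside theirs.

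**Step 3: size for a determinant.** Bias = (difference in loss between levels) × delta. For an assumed 20-point difference this is 0.20 × 0.1 = 0.02, 0.20 × 0.2 = 0.04 and 0.20 × 0.3 = 0.06. In the first simulation (40% loss, delta 0.2) the true coefficient was −0.127, and both methods gave −0.087. In the second (31% v 47% lost), a determinant with no effect received −0.005 to −0.025.

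The 95% half-width for a 50/50 determinant is 1.96 × 2 × 0.4/√960 = 0.051. Most of these biases are inside it; only the 0.06 exceeds it.

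**The case against.** The case on the other side has five parts.

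- **The protocol does not predict this bias.** A reader might infer that it expects families who leave to do worse and to go missing. The text does not support that. Statistical analysis says only that missing data will grow. The Background sentence concerns completing an intervention, not missing study data, and Data collection separates the two by planning research visits and chart retrieval. A completer difference is also compatible with missing at random if earlier BMI z-scores and attendance explain it. This stands.
- **Agreement is not guaranteed.** A reader might infer that the imputation check is empty. It is not. An imputation model may use auxiliary variables (waist, cardiometabolic measures, clinical status, adherence) that make the assumption more plausible. It also retains children with missing values among the 41 determinants, whom a multilevel model would normally drop. This stands, and it is a reason to keep imputation.
- **Detail may sit elsewhere.** The imputation model and any departure from missing at random could be in an analysis plan that is not shown, and delta-adjusted imputation is itself multiple imputation, so the wording does not exclude it. This stands in part. The criticism is not that detail is absent. It is that the article assigns a method to a stated purpose, and in its ordinary form that method cannot serve this purpose for missing outcomes.
- **The sizes are assumed.** Every delta, loss difference and variance used above is an assumption, and 40% is the worst of three scenarios. This stands.
- **The primary hypothesis concerns determinants**, where the effect is smaller and mostly within sampling error. This stands and lowers the priority.

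**Conclusion.** The point holds in a limited form. Multiple imputation is the only listed check for missing data. For missing BMI z-scores, ordinary imputation from the same variables shares the missing-at-random assumption of the multilevel model, so agreement between them is weak evidence about outcome-dependent loss.

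The possible bias in mean change runs from 0.015 to 0.12 z over 15–40% loss and an assumed delta of 0.1 to 0.3 z. The loss that counts is what remains after research visits and chart retrieval, which may be below the planning figures. For determinant coefficients the effect is smaller and arises only where loss differs between levels.

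The documents do not show that such bias will occur or how large it would be. They give enough reason, in the completer evidence and the dropout allowance, to examine it. This is a cheap improvement, not a fault that invalidates the analysis.

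**What to change.** Keep multiple imputation as planned, as the delta = 0 case; it also serves missing determinants and can use auxiliary variables. Add a delta-adjusted imputation:

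- Shift the imputed BMI z-scores that are still missing after research visits and chart retrieval over a pre-stated range, for example 0, 0.1, 0.2 and 0.3 z worse. The range is an assumption and should be labelled as one.
- Apply the shift to all such children, and separately only to those no longer active in the program.
- Report how mean change and the main determinant coefficients move across the range.

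In the text, one sentence under Statistical analysis and one entry in Table 1 are enough. The cost is a few lines of analysis code and no new data. The downside is one more results table and possibly a weaker statement about sustained change.

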### Statistical power

Given a sample size of 1,600 and 41 variables or determinants to be included, the ratio of participants to variables is 39:1. Previous studies have shown that a fitted regression model is likely to be reliable and stable when the number of independent predictors is less than the total sample size divided by 20 [40]. Considering 40%, 25% or 15% dropout (n = 960, 1,200, 1,360 respectively), a two-sided test with significant level α = 0.05/4 = 0.0125 gives 90% power to detect a small R-square 0.0313 -0.0442 for 41 determinants. Thus, we have high power to test the effects of the described variables. For secondary hypothesis one (Table 1), we intend to examine three additional outcomes. To account for multiple hypothesis testing two-tailed α = 0.0125, we will continue to have power exceeding 90% to examine the influence of the determinants on the outcome at one year. For secondary hypothesis two, we intend to examine the determinants for sustainability of weight loss. To do so, we will examine the determinants for maintenance or decline of BMI z-score from year one to year two. If we conservatively estimate that at least 30% will have an increase in BMI z-score over that time period, we have 90% power to detect a variable that will increase this by 1.3 fold – and this is true even if we have 40% drop out from our study. Similarly, if the proportion of participants whose BMI z-score increases from year one to year two is higher, our power would be > 90%. Findings from several published trials suggest these assumptions are appropriate [21,41]. For secondary hypothesis three, we will examine the determinants of program drop out within one year of enrollment. We are sufficiently powered to detect an OR of 1.2 if 25% or more of those who commence a program drop out, and to detect an OR of 1.3 if only 15% drop out of the program.

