**Table 1 T1:** **Objectives**, **hypotheses**, **measures**, **and methods of analysis**

**Objective**	**Hypothesis**	**Outcome measure ****(C = ****Continuous; ****B = ****Binary)**	**Methods of analysis**
**Primary**	Change in BMI z-score will be influenced by child/youth, family, and program characteristics consistent with our theoretical model	BMI z-score (C)	Hierarchical/multilevel modeling
Document changes in anthropometric, lifestyle, behavioural, and obesity-related co-morbidities in children enrolled in Canadian pediatric weight management programs over a three-year period			
**Secondary**	Change in cardiometabolic health outcomes will be influenced by child/youth, family, and program characteristics consistent with our theoretical model	Systolic and diastolic blood pressure (C)	Hierarchical/multilevel modeling
1) Document changes in anthropometric, lifestyle, behavioural, and obesity-related co-morbidities in children enrolled in Canadian pediatric weight management programs over a three-year period;			
		Blood glucose (Fasting & 2 hr post glucose load) (C)	
		Total cholesterol/HDL-C ratio (C)	
		Triglyceride (C)	
		Fitness (C)	
		Quality of Life (C)	
		Lifestyle behaviours (C)	
2) Characterize the individual-, family-, and program-level determinants of change in anthropometric and obesity-related co-morbidities;	Individual-, family-, and program-level determinants will be identified that predict sustainability of change from years 1 – 3.	BMI z-score (C)	Hierarchical/multilevel modeling
3) Examine the individual-, family-, and program-level determinants of program attrition.	Individual-, family-, and program-level determinants will differentiate those who dropped out of the program	Drop out from the program between enrollment and 1 year (B)	Hierarchical/multilevel modeling
			Logistic regression
**Exploratory analyses**	We will identify interaction terms between some individual, family and program determinants	All outcomes	Hierarchical/multilevel modeling
Identify what works best for what groups of individuals or families			
**Sensitivity analyses**	As above	All outcomes	1) Analysis with multiple imputation
1) Imputation methods			
2) All outcomes analyzed simultaneously to account for correlation among them			2) MANCOVA
			3) GEE
3) Serial correlation of all outcomes over time			

*MANOVA*: multivariate analysis of covariance.

*GEE*: Generalized estimating equations.

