### Secondary hypotheses

1. Individual-, family-, and program-level determinants will influence changes in anthropometric, lifestyle behaviour and cardiometabolic health measures over a three-year period.

2. Individual-, family-, and program-level determinants will influence the sustainability of change in BMI z-score over a three-year period.

3. Individual-, family-, and program-level variables will predict program attrition.

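### Secondary hypotheses one and two are stated over three years, but hypothesis one is powered at one year and hypothesis two as a binary outcome from year one to year two

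*Protocol article*

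**What the plan says.** Under Secondary hypotheses, the determinants "will influence the sustainability of change in BMI z-score over a three-year period". Table 1, secondary objective 2, says that determinants "will be identified that predict sustainability of change from years 1 – 3", marks the outcome BMI z-score as continuous, and names hierarchical/multilevel modelling. The only outcome that Table 1 marks as binary is programme drop-out in the first year, under objective 3.

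The Statistical power section describes hypothesis two differently: "we will examine the determinants for maintenance or decline of BMI z-score from year one to year two". It assumes that "at least 30% will have an increase in BMI z-score over that time period" and claims 90% power for a variable that raises this proportion 1.3-fold, even with 40% drop-out. It describes the target as keeping weight off once lost, but it counts participants and removes only those who drop out.

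Hypothesis one also covers a three-year period. Its power is said to exceed 90% "to examine the influence of the determinants on the outcome at one year". BMI is to be collected at baseline and at 6, 12, 24 and 36 months (Data collection).

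**The concern.** The same hypothesis has two windows (years 1 to 3, or year one to year two) and two scales (a continuous z-score, or rise against no rise). The Statistical analysis section reports coefficients for continuous outcomes and odds ratios for binary ones, so the article does not settle which estimate will be the result for hypothesis two. If this stays open, window and scale could be chosen after the data are seen.

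The power statement is affected directly. The 36-month visit plays no part in the powered outcome, although sustained change beyond 12 months is one of the questions that the Background gives as motivation. A reader who takes the 90% as support for the three-year claim is relying on a figure for a different analysis. The same applies to hypothesis one, whose one-year power says nothing about three years.

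There is also a mismatch of wording. Keeping weight lost concerns children who lost some. Sustainability of change, the term in Table 1 and in the hypotheses, concerns everyone.

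**Working it through.** **1. The places side by side**

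| Place | Window | Scale | Target |
|---|---|---|---|
| Secondary hypotheses, no. 2 | three years | BMI z-score, type not stated | change |
| Table 1, secondary objective 2 | years 1 to 3 | continuous, multilevel model | change |
| Statistical power, hypothesis two | year one to year two | rise or no rise | weight loss, counted in participants |

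**2. Inputs for the stated 90%**

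From Statistical power: n = 1,600 × 0.60 = 960, proportion rising p = 0.30, effect 1.3-fold. No alpha is given for hypothesis two. The section uses 0.05/4 = 0.0125 for the primary analysis and for hypothesis one. The Statistical analysis section requires two-sided tests at 0.05, with Bonferroni adjustment for secondary outcomes. Whether 1.3 is an odds ratio or a risk ratio, and how the predictor is distributed, is not stated.

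**3. Reproducing the 90%**

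For logistic regression on a continuous predictor (Hsieh's formula):

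power = Φ(√(n·p·(1−p)) × ln(OR) − z)

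- √(960 × 0.30 × 0.70) = √201.6 = 14.20, and ln(1.3) = 0.2624. The product is 3.725.
- Two-sided alpha 0.0125, z = 2.498: Φ(1.227) = **89.0%**.
- Two-sided alpha 0.05, z = 1.960: Φ(1.765) = 96.1%.

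Other readings with all 960 children:

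| Reading | alpha 0.05 | alpha 0.0125 |
|---|---|---|
| Evenly split binary factor, 30% vs 39% (risk ratio 1.3) | 83.6% | 66.9% |
| Evenly split binary factor, odds ratio 1.3 | 47.8% | 27.7% |

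A one-sided test at 0.05 on 30% vs 39% gives 90.2%, but it would contradict the two-sided rule. So the figure fits, approximately, an odds ratio of 1.3 per SD for a binary outcome at two-sided 0.0125. It is not an arithmetic error.

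**4. The analysis in Table 1**

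For a continuous outcome the detectable effect is an R-square. In a single-level approximation with one predictor, 90% power at two-sided 0.0125 needs a noncentrality of about (2.498 + 1.282)² = 14.29, so R-square ≈ 14.29/(n + 14.29):

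- n = 960: 14.29/974.29 = **0.0147**.
- At alpha 0.05: (1.960 + 1.282)² = 10.51, and 10.51/970.51 = 0.0108.

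**5. Dependence on year-three retention**

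The protocol gives 15%, 25% and 40% drop-out without tying them to a visit, and the Statistical analysis section expects missing data to grow with time. The two lower rows are assumptions that show the range. At alpha 0.0125:

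| Children retained | Share of 1,600 | R-square for 90% power, one predictor |
|---|---|---|
| 1,360 | 85% | 0.0104 |
| 1,200 | 75% | 0.0118 |
| 960 | 60% | 0.0147 |
| 672 | 42% (assumed) | 0.0209 |
| 480 | 30% (assumed) | 0.0291 |

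No three-year power can be stated for either hypothesis until a year-three retention is chosen.

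**The case against.** The article condenses a fuller protocol, and a power paragraph often uses a simplified outcome. BMI z-score is collected to 36 months, Table 1 already names a continuous analysis over years 1 to 3, and the primary hypothesis is untouched. A continuous outcome usually carries more information than a rise/no-rise split, so the tabulated analysis may be well powered. All of this is fair and limits the weight of the point. It does not remove the conflict: the power text says what will be examined, and that differs from Table 1 in window and in scale.

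A reader might go further and infer that the analysis includes children who never lost weight, that regression to the mean therefore makes determinants of early success look like determinants of relapse, and that it should be restricted to children whose z-score had fallen by year one. The documents do not support this, for two reasons.

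- The denominator is an inference. The text speaks of participants and removes only drop-outs, but it neither states nor excludes a restriction. The arithmetic cannot decide: at two-sided 0.05, a subset of 727 would also reach 90% with an odds ratio of 1.3 per SD.
- The bias runs the other way. Take a stable level plus autocorrelated fluctuation (SD 0.3, correlation 0 to 0.8) and a determinant that causes a lasting fall of 0.1 per SD in year one and nothing afterwards (all assumed). In simulation, its odds ratio for a rise in year two is 1.00 in the full cohort but 0.88 to 0.95 among year-one losers. A continuous model in those losers, adjusted for baseline and 12-month z-score, also gives a false coefficient, about −0.05 to −0.01 per SD. Restriction would create a spurious association that the unrestricted comparison does not have.

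**Conclusion.** The point holds for window and scale, which conflict explicitly. The 90% for hypothesis two belongs to a binary outcome from year one to year two, not to the continuous years 1 to 3 analysis in Table 1. Hypothesis one is a three-year hypothesis with power claimed only at one year. The mismatch between weight loss and change is one of wording and needs clarifying; it is not evidence of a biased analysis.

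The 89.0% reproduction assumes an odds ratio per SD and alpha 0.0125, neither of which is stated for hypothesis two. The R-square of 0.0147 assumes 960 children, one predictor, alpha 0.0125 and no clustering by centre. The issue concerns secondary hypotheses in an observational registry. It should be corrected before analysis, but it does not threaten the primary hypothesis.

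**What to change.** - Keep the Table 1 analysis for hypothesis two: continuous BMI z-score over years 1 to 3 in the multilevel model, using the planned 24- and 36-month data. Delete the binary year-one-to-year-two version from Statistical power.
- Refer to sustainability of change in all participants throughout, without restricting to children who lost weight in year one.
- Restate the power for that analysis as a detectable R-square, with the alpha and the year-three retention stated.
- For hypothesis one, either give power at three years under the same retention or limit the power claim to one year.

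The cost is wording in Statistical power, with Table 1 and Secondary hypotheses checked for agreement, plus one recalculation that may be less favourable than the present figure. No new data are needed.

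### The power statements for secondary hypotheses 2 and 3 hold only for an odds ratio per SD of a continuous determinant, and the text applies them to any variable

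*Protocol article*

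**What the plan says.** All of this is in the Statistical power section of the protocol article unless noted.

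- **Secondary hypothesis 2 (sustained change).** At least 30% of children are expected to have a rise in BMI z-score from year one to year two. Against that base, "we have 90% power to detect a variable that will increase this by 1.3 fold". The text adds that this stays true with 40% dropout, which an earlier sentence equates with n = 960.
- **Secondary hypothesis 3 (attrition within one year).** "We are sufficiently powered to detect an OR of 1.2 if 25% or more of those who commence a program drop out"; an OR of 1.3 is said to be detectable if only 15% drop out. No power figure is attached.
- **Alpha.** The overall R-square calculation reads "a two-sided test with significant level α = 0.05/4 = 0.0125 gives 90% power to detect a small R-square 0.0313 -0.0442 for 41 determinants". The same 0.0125 is repeated for secondary hypothesis 1 but not for hypotheses 2 and 3. The Statistical analysis section sets two-sided tests at 0.05 and adds: "The Bonferroni method will be used to adjust the level of significance for testing for secondary outcomes".
- **Determinants.** The Measurements section lists continuous items (age, baseline BMI z-score, clinic hours) alongside binary ones (sex, immigrant status, individual versus group care).
- **Model stability.** "Given a sample size of 1,600 and 41 variables or determinants to be included, the ratio of participants to variables is 39:1", set against a rule that "the number of independent predictors is less than the total sample size divided by 20".

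**The concern.** The wording for hypothesis 2 refers to a proportion of 30% and to a variable that raises it 1.3-fold. Read plainly, that is 30% against 39% between children with and without a characteristic. That comparison does not have 90% power at n = 960, and for a binary determinant the attrition odds ratios fall much further short. For these two hypotheses the section gives no effect scale, determinant type or alpha.

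What is at stake is how null results are read. The study sets out to learn which individual, family and program features go with sustained change and with dropping out. If group care or immigrant status shows no significant association with attrition, a reader relying on this section would take it as a well-powered negative. At the stated odds ratios the chance of detecting a true association for such a determinant is one half at best.

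**Working it through.** **Inputs from the protocol article.** N = 1,600; n = 960 at 40% dropout; event proportion 30% (hypothesis 2); program dropout 25% or 15% (hypothesis 3); effects 1.3-fold, OR 1.2 and OR 1.3; two-sided tests; alpha 0.05 (z = 1.960) or 0.0125 (z = 2.498).

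**Assumptions.** Prevalence of a binary determinant is 50% (the most favourable) or 20%. The stated event proportion is that of the reference group. All 1,600 children contribute to hypothesis 3. Clustering by centre is ignored, and so is correlation between determinants unless stated.

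**1. The plan's own R-square figures.** With a noncentral F test, 41 predictors, alpha 0.0125 and 90% power, the detectable R-square is 0.0439 at n = 960 and 0.0311 at n = 1,360. The plan gives 0.0442 and 0.0313, so that part reproduces.

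**2. The reading on which the hypothesis 2 and 3 claims nearly reproduce.** For an odds ratio per SD of a normal determinant, power = Φ(√(n·p·(1−p))·ln OR − z).

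- Hypothesis 2: √(960×0.30×0.70) = 14.199; × ln 1.3 (0.2624) = 3.725. Power is Φ(1.765) = 96.1% at 0.05 and Φ(1.227) = 89.0% at 0.0125. A 6,000-run logistic simulation gave 96.1% and 88.3%.
- Hypothesis 3, OR 1.2 at 25%: √(1,600×0.25×0.75) = 17.321; × 0.1823 = 3.158. Power is 88.5% at 0.05 and 74.5% at 0.0125.
- The same at 30% dropout: 18.330 × 0.1823 = 3.342, which gives 80.1% at 0.0125.
- Hypothesis 3, OR 1.3 at 15%: √(1,600×0.15×0.85) = 14.283; × 0.2624 = 3.747. Power is 96.3% at 0.05 and 89.4% at 0.0125.

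This reading is not stated in the text. It is also optimistic: if the other determinants explained 20% of the variance of the one tested (an assumption), hypothesis 2 at 0.0125 would fall from 89.0% to 79.8%.

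**3. A binary determinant, hypothesis 2, n = 960, 30% versus 39%.** Power = Φ((Δ − z·s₀)/s₁), where s₀ is the pooled and s₁ the unpooled standard error.

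- 480 versus 480: Δ = 0.09; s₀ = √(0.345×0.655×2/480) = 0.03068; s₁ = 0.03055. At 0.05, Φ((0.09 − 0.0601)/0.03055) = 83.6%. At 0.0125, Φ((0.09 − 0.0766)/0.03055) = 66.9%.
- 192 versus 768 (20% prevalence): s₀ = 0.03758, s₁ = 0.03889; 66.3% and 46.1%. The unpooled formula gives 2 to 3 points less here.
- If 1.3 is an odds ratio, balanced: 47.8% and 27.7%.

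**4. A balanced binary determinant, hypothesis 3, 800 versus 800.**

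| Scenario | Proportions | Power, alpha 0.05 | Power, alpha 0.0125 |
|---|---|---|---|
| OR 1.2, 25% dropout | 0.250 vs 0.286 | 36.4% | 18.8% |
| OR 1.3, 15% dropout | 0.150 vs 0.187 | 49.9% | 29.4% |

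**5. What is detectable for a binary determinant.** Solving the formula in step 3 for the effect, at alpha 0.05; each range runs from 80% to 90% power.

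| | 50% prevalence | 20% prevalence |
|---|---|---|
| Hypothesis 2, n = 960, ratio of proportions | 1.29–1.33 | 1.36–1.41 |
| Attrition 25%, n = 1,600, OR | 1.37–1.43 | 1.47–1.56 |
| Attrition 15%, n = 1,600, OR | 1.45–1.53 | 1.56–1.68 |

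**6. Events in the attrition model.** At 25% dropout there are 0.25×1,600 = 400 events, and 400/41 = 9.8 per determinant. The 39:1 ratio counts children, not events.

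**The case against.** The strongest reply is that the authors probably used a standard logistic power formula for a continuous covariate, and on that basis two of the three claims come within about one point of 90% even at 0.0125. This stands. A reader might infer that the figures fail generally at the Bonferroni level; they do not. Only OR 1.2 at exactly 25% dropout falls short there. Whether 0.0125 governs hypothesis 3 is not stated, the phrase sufficiently powered carries no figure to contradict, and the claim covers dropout of 25% or more. The Background cites attrition of 27–73%.

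Hypothesis 2 is also shown here at the plan's worst case. With 25% dropout (n = 1,200), a balanced binary determinant with 30% versus 39% has about 91% power at 0.05. But the text makes its 90% claim expressly for 40% dropout.

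Two further readings are tempting and unsupported. One is that the 39:1 ratio breaks the plan's own rule. The rule is written on total sample size and is met even at n = 960 (960/41 = 23.4). The other is that two over-fitted logistic models are planned. Table 1 gives hypothesis 2 a continuous BMI z-score outcome under hierarchical modelling and names logistic regression only for attrition, and the document sets no events-per-variable threshold. At most, the 39:1 ratio says nothing about events in that one attrition model.

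Finally, a condensed article may leave effect scales to the full protocol. That would excuse silence, but this section prints a specific 90% and a sufficiency claim without restriction, so the printed claims can be checked.

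**Conclusion.** The point holds in a limited form. The power claims for secondary hypotheses 2 and 3 are approximately right for an odds ratio per SD of a continuous determinant that is uncorrelated with the others. They are wrong for binary determinants, which the plan will also test. The shortfall for a balanced binary determinant is moderate for hypothesis 2 (84% or 67% against a stated 90%) and large for attrition (36% or 19%, and 50% or 29%). It widens as prevalence moves away from 50%.

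These figures rest on the assumed prevalences, on reading the stated proportion as the reference-group rate, and on ignoring clustering. The primary R-square calculation is not affected. This is a correction worth making to the secondary hypotheses; it does not undermine the study.

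**What to change.** In the Statistical power section:

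1. Restate the hypothesis 2 and 3 effects as odds ratios per SD of a continuous determinant, give the alpha used for each, and limit the 90% and sufficiency claims to that case.
2. Replace the sufficiency wording with power figures. For OR 1.2 at 25% dropout these are 88.5% at alpha 0.05 or 74.5% at 0.0125, with 80% reached at about 30% dropout.
3. Add the detectable effects for binary determinants at 50% and 20% prevalence from step 5 of the working, or the larger values if 0.0125 applies.
4. Optionally, note that the 39:1 ratio counts participants and that the attrition model has about 10 events per determinant at 25% dropout.

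The cost is a few sentences and less favourable stated figures. No extra patients, visits or data are needed.
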